## Abstract

**Introduction:**

Stroke survivors, once in the community, face challenges with their long-term rehabilitation care and present higher levels of loneliness, depression and anxiety than the rest of the population. A community-based performance arts programme, Stroke Odysseys (SO), has been devised to tackle the challenges of living with stroke in the UK. In this study, we aim to evaluate the implementation, impact and experiences of SO for stroke survivors.

**Methods and analysis:**

Scaling-up Health Arts Programmes: Implementation and Effectiveness Research (SHAPER)-SO aims to scale-up SO to 75 participants and 47 stakeholders, while simultaneously evaluating the effectiveness and implementation of the programme. The main research aim is to evaluate the implementation, effectiveness, impact and experiences of a community-based performance arts programme (SO for stroke survivors). This mixed-methods study will evaluate the experience and impact of SO on those participating using mixed methods (interviews, observations and surveys) before and after each stage and carry out non-participant observations during a percentage of the workshops, training and tour. Data will be analysed using quantitative and qualitative approaches. This is a study within the SHAPER programme.

**Ethics and dissemination:**

Ethical approval has been granted by the King’s College London PNM Research Ethics Panel, REC reference: LRS/DP-20/21–21549. Written informed consent will be sought for participants and stakeholders. The results of the study will be reported and disseminated at international conferences and in peer-reviewed scientific journals.

**Trial registration number:**

NCT04864470.

Strengths and limitations of this studyThe first study examining an art intervention on stroke survivors, using a type 2 hybrid design, with a dual focus on effectiveness and implementation outcomes.The unique study design will result in a package of clinical and implementation data on this particular intervention.There may be inconsistency in participant experience throughout an intervention period if in-person sessions are switched online and vice versa due to COVID-19 social distancing restrictions.Access to the COVID-19-adapted online delivery of Stroke Odysseys may be challenging for people with severe acquired brain injury, resulting from stroke.

## Introduction

Stroke affects over 113 000 people every year^1^ and, according to the latest statistics, there are currently more than 1.2 million stroke survivors in the UK.^2 3^ The effects of stroke are often devastating, with almost two-thirds of survivors leaving the hospital with a disability and half experiencing depression within 5 years.^4 5^ In addition to the substantial impact, stroke has on those affected and their caregivers, it can also pose a significant financial burden to health and social care services. The societal cost of stroke has been estimated to be £26 billion per annum, with National Health Service (NHS) costs accounting for £3.4 billion in 2015, and projected to increase to £10.2 billion by 2035.^6^

Stroke survivors commonly face emotional, social and psychological challenges, with depression, anxiety and apathy being the most prevalent neuropsychiatric sequelae.^7^ Such disabling symptoms are often coupled with feelings of abandonment^8^ once hospital rehabilitation ends and their recovery plateaus. Stroke survivors in the UK usually receive rehabilitation while in hospital but once they are discharged, the level of support in the community tends to be variable and in the long-term, inadequate for their needs.^8^ This is consistent with a meta-review of qualitative systematic reviews,^9^ which reported a lack of self-management resources available following stroke, highlighting the gap between available services and the long-term social, emotional and physical needs of stroke survivors throughout their rehabilitation journey.^10^ Additionally, the findings of a survey by the Stroke Association in the UK emphasised the devastating burden and ‘hidden effects’ of stroke.^11^ The survey, which collated data from over 10 000 stroke survivors and is the biggest to date in the UK, revealed that the effects of stroke on cognition, emotions, relationships and mental health are widespread, can be life-long and are often overlooked or neglected. In the survey, 50% of stroke survivors and 85% of caregivers reported a gap between the support provided versus the support they felt was needed. While current stroke rehabilitation targets functional recovery, it fails to meet the psychosocial needs of stroke survivors.

The evidence summarised above suggests that there is a need for more holistic rehabilitation programmes, especially non-pharmacological and non-invasive modalities, to address the psychosocial needs and improve the quality of life of stroke survivors.^12^ Arts-based programmes (such as ‘Stroke Odysseys (SO)’ discussed below) are one such approach that shows promising results in enhancing the well-being, self-esteem, social life and rehabilitation experiences of patients with stroke.^13^ Indeed, over the past decade, several studies conducted in this patient population have consistently shown a positive impact of different art modalities on psychological (eg, enhancement in confidence and a better sense of control), social (eg, increased social interactions and peer support) and functional (eg, improvement in physical abilities) outcomes.^12^

Nonetheless, despite the growing body of research on the benefits of art interventions, the process of scaling-up these interventions, embedding them into healthcare and its associated challenges are not yet well established. Preliminary data indicate that SO (discussed below) is received positively by those who take part,^14^ however, identifying barriers to implementation and exploring ways to overcome these obstacles are essential to successfully and sustainably embed SO into clinical pathways and roll out the programme at a wider scale.

SO is part of the Scaling-up Health Arts Programme: Implementation and Effectiveness Research (SHAPER), which is, to our knowledge, the world’s largest study on arts and health examining both clinical effectiveness and implementation effectiveness of three community-based arts programmes: Melodies for Mums (M4M), a singing intervention for postnatal depression, PD-Ballet, a dance intervention for Parkinson’s Disease and SO. Overall, SHAPER has three primary aims: (1) to successfully embed each of the art interventions into the healthcare system (ie, taking a social prescribing approach), (2) to scale up these interventions at a larger scale and (3) to facilitate these interventions being commissioned by Clinical Commissioning Groups (CCGs), ensuring the long-term sustainability of delivery.^15^

### Stroke Odysseys

Rosetta Life, a well-established non-profit organisation with a track record of conducting arts programmes for stroke and brain injury survivors, developed SO, a performance-based arts programme with continued consultation from stakeholders (including stroke survivors). SO provides an opportunity for those who have had a stroke or brain injury to share their experiences with an audience through movement, music, songwriting and the spoken word. The programme, which has now been running for over 21 years, uses performance arts to help stroke survivors overcome psychological challenges such as lowered self-esteem, anxiety and depression, which are commonly reported by individuals.^16^

In this protocol paper, we present our plans to evaluate. SHAPER-SO will be a two-pronged study, examining the implementation and clinical effectiveness of SO. The research we will be undertaking examines both, the impact of performance arts on participants and how SO can be embedded into clinical pathways. This will help us to identify not just ‘if’ but also ‘why’ the programme works and support our understanding of how it can be successfully delivered and scaled up within clinical pathways. Alongside this, we will examine participants’ experiences of the programme using an ethnographic and constructivist approach. To the best of our knowledge, SHAPER-SO is the first study of its kind in the context of stroke care and rehabilitation.

## Aims and objectives

The three main objectives in this study are: (1) to explore the clinical impact (effectiveness) of SO on stroke survivors; (2) to explore SO implementation aspects including uptake, adoption, perceived acceptability, appropriateness, feasibility, the fidelity of receipt, unintended consequences and sustainability and (3) to evaluate implementation costs and cost-effectiveness of the intervention, with focus on the costs associated with implementing SO into existing care pathways, health services, partner organisations and commissioning and the impact of scaling up SO on the utilisation of health services.

The main research aim is to evaluate the implementation, effectiveness, impact and experiences of a community-based performance arts programme (SO for stroke survivors).

Our study objectives are as follows:

To explore the impact of participation in performance programmes on cognitive health and physical, psychological and social well-being of people who have experienced stroke.To study the context, mechanisms of delivery and interactions between participants and facilitators which take place during SO delivery.To explore the learning and experiences of facilitators and participants after SO delivery.To evaluate any change in the emotional well-being, participation and activity of stroke participants pre-SO and post-SO.To evaluate the extent to which SO is acceptable, feasible to undertake and appropriate to survivors and wider stakeholders (including ambassadors, artists, and clinician referrers to the programme).To explore the challenges, barriers, facilitators and unintended consequences of the implementation of SO.To assess the costs associated with the implementation of the programme.To assess the adoption, adherence to it and attrition rates of the programme.

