## Methods and analysis

### Design

SHAPER-SO is a mixed-methods programme study, comprising quantitative and qualitative methods to assess the clinical and implementation outcomes outlined in the measures section below.

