### Outcomes

Data on the clinical outcomes will be collected from stroke survivors who have enrolled on the SO programme (see table 1). Data on the implementation outcomes will be collected from stroke survivors who have enrolled on the SO programme as well as the wider stakeholder group involved in the SO programme, including deliverers, referrers and supporters (see table 2).

Time points for data collection: T0—baseline; T1—midway through the 12-week programme (weeks 5–7); T2—immediately postperformance (12–14 weeks); T3—immediately after the advocacy training for stroke ambassadors.

To maximise inclusivity and outcome completion, and minimise participant burden, outcome assessments, where possible, will be conducted either face-to-face, online, by telephone or via postal questionnaire depending on the outcome measures being assessed, participants’ preferences and government COVID-19 guidelines.

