### Assessment descriptions for clinical outcomes

#### Qualitative assessments

##### Ethnographic research

Ethnographic non-participant observations of a selection of the 12 workshops including at least 1–2 groups from each of the two phases (building confidence, rehearsal and production) to capture facilitator and participant practice, interactions and routines. Each observation period will last for the duration of the workshop, and the ethnographic researcher will record field notes contemporaneously.

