### Assessment descriptions for the implementation outcomes

#### Quantitative assessments

Validated and standardised implementation scales will be used to gather quantitative data on how acceptable, appropriate and feasible the SO programme is perceived by stroke survivors, ambassadors, deliverers, supporters and referrers. These scales include the Acceptability of Programme Measure (AIM), the Programme Appropriateness Measure (IAM) and the Feasibility of Programme Measure (FIM). For further information on the development of these scales, please refer to the paper by Weiner *et al*.^24^

The implementation science researchers will quantify and cost the resources used in implementing the programme, evaluate wider service utilisation and associated costs before and after participants complete the programme, including any changes to their quality-of-life profile measured using the EQ5D-3L preference-based QoL measure. The EQ5D-3L is a self-complete multiattribute measure of health-related quality of life that assigns individuals a unique state of health based on their response to individual items. Each unique health state is associated with a predetermined ‘utility’ value derived from a survey of wider community preferences over different states of health. The utility scale is anchored at 1 (full health) and zero (death), with negative values allowed in instances where states of health are considered worse than death. Health state utility values are subsequently used to estimate quality-adjusted life years (QALYs) survived over time—the utility scores providing the means of making the quality adjustments. Evidence on costs and QALYs will subsequently be used to inform an analysis of the cost-effectiveness of programme delivery at scale.

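### Effectiveness and cost-effectiveness are main objectives of a single cohort with no comparator, and Table 2 schedules no baseline EQ5D or AD-SUS

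*Protocol article*

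**What the plan says.** **Claims.** Under Aims and objectives, main objective (1) is "to explore the clinical impact (effectiveness) of SO on stroke survivors" and main objective (3) is "to evaluate implementation costs and cost-effectiveness of the intervention". The fourth item in the study-objectives list is "To evaluate any change in the emotional well-being, participation and activity of stroke participants pre-SO and post-SO". The strengths and limitations box describes the study as "using a type 2 hybrid design, with a dual focus on effectiveness and implementation outcomes". The Stroke Odysseys section adds that the research will help show whether the programme works as well as why. Under Quantitative assessments, costs and QALYs are to "inform an analysis of the cost-effectiveness of programme delivery at scale".

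**Design.** The Design section says "SHAPER-SO is a mixed-methods programme study, comprising quantitative and qualitative methods to assess the clinical and implementation outcomes". Under Outcomes, "Data on the clinical outcomes will be collected from stroke survivors who have enrolled on the SO programme". No other source of clinical data is named.

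**Measures.** The clinical assessment descriptions carry only a qualitative heading, covering "Ethnographic non-participant observations of a selection of the 12 workshops" and semistructured interviews. The Data collection section confines the quantitative methods to experiences of, and attitudes to, the programme and its implementation. The Quantitative analysis section names AIM, FIM, IAM and EQ5D.

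**Timing.** Table 2 gives EQ5D-5L and AD-SUS at T2 and T3. The Quantitative assessments text names EQ5D-3L and describes service use and costs before and after the programme. The Quantitative analysis section also plans a before/after comparison of EQ5D.

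**The concern.** Effectiveness and cost-effectiveness are both comparative ideas. The first asks how participants fared relative to how they would have fared without SO; the second asks for extra cost and extra health relative to some alternative. With one cohort and no stated counterfactual, a before/after change mixes any programme effect with recovery, regression to the mean, other care and the selection of people willing to commit to 12 weeks.

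The stakes are practical. The Introduction ties the wider SHAPER programme to commissioning, so a favourable EQ5D change reported under the label of effectiveness or cost-effectiveness could inform funding. The limitations listed in the article concern COVID-19 switching and online access; the absence of a comparator is not among them.

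The more modest alternative, an uncontrolled change from baseline, is also insecure, because the only schedule shown for EQ5D and AD-SUS omits T0.

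**Working it through.** **1. The plan's own figures.** Sampling gives 75 survivors and 20% drop-out: 75 × (1 − 0.20) = 60, which reproduces the stated 60. That 60 is the number expected to complete ambassador training (T3). It is not a stated number of T0–T2 pairs. The 75 is a recruitment forecast; the article gives no alpha, power, effect size or SD, so there is no power calculation to reproduce.

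**2. What each claim needs and what is provided.**

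| Claim | Needs | Provided |
|---|---|---|
| Effectiveness of SO | Outcome without SO, observed or assumed | Enrolled cohort only |
| Cost-effectiveness | A stated alternative with its costs and QALYs | Costs and QALYs for the cohort; no alternative named |
| Change in utility and service use | Values at T0 and T2 | Table 2: T2 and T3; text: before and after |
| Change in well-being, participation, activity | Scale or interviews, before and after | Interviews before and after; no scale in visible text |

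**3. What the Table 2 schedule allows.** T2 is immediately after the performance and T3 immediately after ambassador training. Taking T3 − T2 covers only the optional training stage. T2 − T0 would cover the 12-week programme, and it has no T0 term.

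**4. Illustration: an uncontrolled paired test with no programme effect.** Inputs: two-sided 5% test, normal approximation, n = 60 or 75 pairs. The 75 assumes no loss; the 60 is borrowed from the T3 figure. The drift δ, in SDs of the change score, is an assumption and appears nowhere in the document.

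Rejection probability = 1 − Φ(1.96 − δ√n) + Φ(−1.96 − δ√n).

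| δ | n = 60 | n = 75 |
|---|---|---|
| 0 | 5% | 5% |
| 0.1 | 12% | 14% |
| 0.2 | 34% | 41% |
| 0.3 | 64% | 74% |

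For example, with δ = 0.2 and n = 60, δ√n = 1.55 and 1 − Φ(0.41) ≈ 0.34.

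Regression to the mean is one possible source of drift. Suppose the cohort enrols 0.25 to 0.5 SD below the mean to which it would regress, with pre/post correlation ρ of 0.5 to 0.7 (both assumed). The expected rise is (1 − ρ) × shift, with standard error √(2(1 − ρ)/n).
- Shift 0.25, ρ = 0.7, n = 60: rise 0.075, SE 0.10, rejection 12%.
- Shift 0.5, ρ = 0.6, n = 60: rise 0.20, SE 0.115, rejection 41%.
- Shift 0.5, ρ = 0.5, n = 75: rise 0.25, SE 0.115, rejection 58%.

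**5. Why the remedy is wording and not a control arm.** At two-sided 5% and 80% power, n per arm = 2(1.96 + 0.842)²/d². An assumed difference of d = 0.5 SD needs 63 per arm, 126 evaluable in total, and 126/0.8 = 158 recruited. Splitting 60 people 30:30 gives 80% power only for 2.802 × √(2/30) = 0.72 SD. A concurrent comparator of useful size does not fit the stated capacity of 75.

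**The case against.** Several points on the other side are fair.

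- **A single-arm mixed-methods design is legitimate for a scale-up study.** Objective (1) says explore, the primary implementation objective is acceptability, and no efficacy test or power claim is made. This stands: the design is not at fault. The labels are, since the hybrid claim and the promise to learn whether the programme works go beyond exploration.
- **A reader might infer that the study has no clinical scale at all.** The document does not support that. In the copy read, the primary row of Table 1 is blank, which may be a conversion loss. The Abstract mentions surveys before and after each stage, and the Patient and public involvement section separates the measures already made aphasia friendly from the implementation measures still to be checked. A condensed article may also leave instruments to the full protocol.
- **A reader might infer that the before/after objective fails without a comparator or a scale.** It asks only about change, and pre and post interviews can answer it in part.
- **A reader might take 12% to 58%, or 12% to 64%, as the expected false-positive rate.** It is not. Eligibility sets no symptom threshold that would select people at a low point, and the drift, shift and correlation values are all assumed.
- **The economic analysis may be planned elsewhere with an external comparator.** That is possible, and no cost per QALY is explicitly promised. But cost-effectiveness is a stated main objective, and the alternative is part of the question being asked.

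None of this explains the Table 2 timing or the two EQ5D versions, which are contradictions within the article.

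**Conclusion.** The concern holds in a limited form and should be fixed.

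- **Firm:** there is one cohort and no comparator. A before/after change cannot be attributed to SO, and a cost-effectiveness result has no stated alternative, although effectiveness and cost-effectiveness sit in two of the three main objectives.
- **Firm:** Table 2 schedules EQ5D and AD-SUS at T2 and T3 only, against before/after wording in two sections. On that schedule even an uncontrolled change from baseline in utility or service use cannot be computed. The EQ5D version also differs between Table 2 and the text.
- **Conditional:** the visible text names no scale for emotional well-being, participation or activity. This depends on what the primary row of Table 1 contains.

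No size can be taken from the document. The rejection rates show only that modest assumed drift would often produce a significant before/after result in a cohort of 60 to 75.

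A reader might go further and conclude that nothing can be learned about outcomes. That is too strong: with T0 confirmed, a descriptive within-participant change and a cost description are both achievable.

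**What to change.** 1. Reword objective (1) and the hybrid claim as estimating uncontrolled within-participant change, and objective (3) as reporting implementation costs with a cost-consequence summary. Add the absent comparator to the limitations.
2. Present a cost per QALY only against a stated counterfactual, for example utility held at its T0 value, and vary that counterfactual in sensitivity analysis.
3. Add or confirm EQ5D and AD-SUS at T0 in Table 2, so that it agrees with the before/after wording in the text. T0 collection should not be taken as already in place; the example in step 2 depends on it.
4. Reconcile EQ5D-5L in Table 2 with EQ5D-3L under Quantitative assessments.
5. Check the primary row of Table 1. If it names scales, carry them into the assessment and analysis sections. If it names none, either use the EQ5D items at T0 and T2 for the before/after objective or state that it is answered qualitatively.

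The cost is a more modest claim, some rewording and, if T0 is not already planned, one more questionnaire administration at an existing contact. No extra recruitment or control arm is needed.

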## Theoretical underpinning

An ethnographic and constructivist approach will be used to examine stroke survivors’ experiences of the SO programme (objective 2). This is described as the study of social interactions, behaviours and perceptions that occurs within groups, team organisation and communities. Ethnography provides rich, holistic insights into people’s views and actions as well as the nature of the location (context) they inhabit. The aim has been described as ‘getting inside’ the way each group of people sees the world.^17^ Ethnography has a strong emphasis on ‘unstructured data and involves implicit interpretation of the meaning and function of human interactions, rather than hypothesis testing. This approach aligns well with the complex nature of the SO programme.

The implementation analyses are informed by several well-established implementation science frameworks, which we have applied to develop a set of implementation facets of SO to assess, both quantitatively and qualitatively (see the Methods). We used the recently developed ‘Implementation Science Research Development’ (ImpRes) framework^17^ to identify the elements of implementation that the study ought to capture, ImpRes defined 10 different domains that an implementation evaluation ought to capture—including capturing stakeholder engagement, the outcome of implementation (eg, how acceptable, appropriate and feasible SO and its implementation processes are to those delivering and also receiving SO) and any unintended consequences (objective 3, 5 and 6). Moreover, we reviewed the Capability, Opportunity and Motivation Model of Behaviour (COM-B) tool^18^ to help us identify any barriers that may affect an individual’s engagement with the SO programme (objectives 7 and 10). The COM-B components lie at the centre of the Behaviour Change Wheel, a framework for designing and characterising behaviour change interventions.^18^ The Consolidated Framework for Implementation Research (CFIR)^19 20^ will help us map reported barriers and drivers to the implementation of the SO (objective 7); and finally, the Reach Effectiveness Adoption Implementation Maintenance model^21 22^ taken together with Proctor *et al*’s^23^ taxonomy of implementation outcomes, guided our choice of implementation measures to assess.

